## Abstract

**Background:**

Acupuncture is widely used for knee osteoarthritis (KOA), despite contradictory evidence. This study is designed to determine the efficacy of electro-acupuncture and manual acupuncture versus sham acupuncture for KOA.

**Methods/design:**

This is a multi-center three-arm randomized controlled trial. It will enroll 480 participants with KOA in China. Participants will be randomly assigned 1:1:1 to receive 24 sessions of electro-acupuncture, manual acupuncture, or sham acupuncture over 8 weeks. The primary outcome is the response rate, which is the proportion of patients who achieve the minimal clinically important improvement in pain and function at 8 weeks. The primary outcome will be analyzed using the *Z*-test with the intention-to-treat set. Secondary outcomes include pain, function, global patient assessment, and quality of life. Full details of the statistical analysis plan for the primary and secondary outcomes will be described in this article. The statistical analysis plan was written and submitted without knowledge of the study data.

**Discussion:**

The data will be analyzed according to this pre-specified statistical analysis plan to avoid data-driven analysis and to enhance the transparency of the trial. The aim of the trial is to provide high-quality evidence on the efficacy of acupuncture for KOA.

**Trial registration:**

Clinicaltrials.gov, NCT03366363. Registered on 20 November 2017.

## Background

Knee osteoarthritis (KOA) is one of the leading causes of chronic pain and disability in older adults [1], with symptomatic KOA affecting 8.1% of Chinese people [2] and 1.6–14.9% of Europeans according to age class [3]. The socioeconomic burden of KOA is large, amounting to between 1.0% and 2.5% of the gross domestic product in developed countries [4].

Since no disease-modifying treatment is available, the current management of KOA is symptomatic [5], often with non-steroid anti-inflammatory drugs. However, these have a limited effect [6, 7]. Although total knee replacement is an effective treatment for symptomatic end-stage disease, approximately 15% of patients have continuing pain and mobility problems after surgery and the lifespan of prostheses is limited [8].

Acupuncture is increasingly used in clinical practice [9], although evidence of its efficacy is contradictory [10, 11]. Acupuncture has a dose–effect relationship [12]. However, the dose of acupuncture administered in several previous trials was far from adequate [13]. The frequency of acupuncture is one of the key factors of a dose [14]. A review suggested that the frequency of acupuncture is usually three to five sessions per week in China, whereas it is mostly one session per week in Europe and America [15]. Based on our previous pilot trial [16], high-dose acupuncture (24 sessions in 8 weeks) may be an effective option for KOA. Electro-acupuncture (EA) combines manual acupuncture (MA) with an electric stimulus [17]. Both EA and MA are frequently used in clinical practice. Therefore, the current trial is designed to evaluate the effect of EA and MA, compared with sham acupuncture (SA), in patients with KOA.

The protocol of the trial has been published previously [18] and provides more detail on the trial rationale, eligibility criteria, and interventions. This article aims to report in detail the statistical analysis plan to reduce the risks of reporting bias and enhance the transparency of the trial. The statistical analysis plan was approved on 30 October 2017 (version 1.0) and drafted without knowledge of any of the results.

## Methods/design

### Study design

This three-arm randomized sham-controlled trial has been approved by the ethics committees at each of the nine participating hospitals. Eligible KOA participants, diagnosed according to the American College of Rheumatology criteria [19], are randomly assigned (1:1:1) to receive 24 sessions of EA, MA, or SA over 8 weeks. The block randomization, with block sizes of 6 and 9, is stratified by study center and is performed via a web-based randomization system. Superficial insertion at non-acupoints with no electric current will be used for the SA group, which is one of the most commonly used approaches for administering sham treatments in acupuncture trials. The nature of acupuncture means that acupuncturists are not blinded to treatment allocation; however, patients, outcome assessors, and statisticians will remain masked. Informed consent will be obtained from each participant before randomization. The trial has been registered with ClinicalTrials.gov (NCT03366363).

### Objectives

The objective of the current study is to determine if EA or MA improve clinical outcomes at 8 weeks in patients with KOA. The following two null hypotheses will be tested:H1: There is no difference in the patients’ response rate between the EA group and the SA group.H2: There is no difference in the patients’ response rate between the MA group and the SA group.

### Outcomes

#### Primary outcome

The primary outcome is the response rate [20], which is the proportion of patients who achieve the minimal clinically important improvement in pain and function at 8 weeks post-randomization. The average pain over the previous week will be assessed using an 11-point numerical rating scale (NRS) [21] with scores ranging from 0 to 10. The minimal clinically important improvement in pain is defined as 2 points in the NRS [11, 22]. The average function over the previous week is measured using the Western Ontario and McMaster Universities Osteoarthritis Index (WOMAC) function subscale [23] with scores ranging from 0 to 68. The minimal clinically important improvement in function is defined as 6 points in the WOMAC function subscale [11, 22]. The criteria for a participant to be a responder are presented in Fig. 1. The response rate is also measured at weeks 4, 16, and 26 after randomization.

**Fig. 1 Fig1:**
[figure not shown]
Responder criteria. WOMAC Western Ontario and McMaster Universities Osteoarthritis Index

#### Secondary outcomes

The secondary outcomes are:Numerical rating scale [21]: an 11-point patient-reported outcome measure (PROM) with scores ranging from 0 (no pain) to 10 (worst pain)WOMAC [23] pain subscale: a 5-item PROM with total scores ranging from 0 to 20; higher scores indicate worse painWOMAC [23] function subscale: a 17-item PROM with total scores ranging from 0 to 68; lower scores indicate better physical functionWOMAC [23] stiffness subscale: a 2-item PROM with total scores ranging from 0 to 8; higher scores indicate more stiffnessPatient global assessment [24]: a 5-point Likert scale12-item Short Form Health Survey (SF-12) [25] physical dimension: total scores range from 0 to 100; lower scores indicate a worse quality of lifeSF-12 [25] mental dimension: total scores range from 0 to 100; higher scores indicate a better quality of life

For the patient global assessment, participants are asked how their knee symptoms were during the past week. Answers can include “extremely improved,” “slightly improved,” “not changed,” “slightly aggravated,” and “extremely aggravated.”

The NRS, WOMAC, patient global assessment, and SF-12 are measured at 4, 8, 16, and 26 weeks after randomization. The blinding assessment is measured at 4 and 8 weeks after randomization. The credibility and expectancy of participants are measured 5 min after the first acupuncture session [26]. The use of rescue medicine is also recorded throughout the trial.

#### Safety outcome

Adverse events are recorded throughout the trial. Based on the potential relationship between acupuncture and adverse events, adverse events are categorized as related to the treatment or not.

### Sample size

Based on the results of our previous trial [16], the response rates for the EA, MA, and SA groups were assumed to be 70%, 60%, and 40%, respectively. With a two-sided significance level of 2.5% and power of 80%, 128 participants in each group will be required to detect a difference as small as 20% between each acupuncture group and the control group. The two-sided significance level of 2.5% is a Bonferroni-adjusted alpha level as per the two predefined primary comparisons: EA vs. SA and MA vs. SA. With an estimated loss-to-follow-up rate of 20%, 480 participants will be recruited in total.

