#### Analysis of the primary outcome

In the analysis of the primary outcome, the response rates of the three groups at 8 weeks will be calculated and the *Z*-test for comparisons of proportions will be used with the full analysis set. Any missing data at 8 weeks will be imputed using the baseline value. There will be two comparisons. The first comparison is that between the EA group and the SA group. The second is that between the MA group and the SA group. The significance level will be adjusted at 0.025 for multiple comparisons using the Bonferroni method.

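### The sample size treats the 20% lost as absent from the analysis, while the primary analysis counts missing week-8 patients as non-responders; the stated 80% power for MA vs SA ignores this dilution

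*SAP article*

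**What the plan says.** The Sample size section takes its planning rates from the group's previous trial: "the response rates for the EA, MA, and SA groups were assumed to be 70%, 60%, and 40%, respectively". It sets power at 80% and explains the test level: "The two-sided significance level of 2.5% is a Bonferroni-adjusted alpha level as per the two predefined primary comparisons". From this it concludes that "128 participants in each group will be required to detect a difference as small as 20% between each acupuncture group and the control group". It then allows for attrition: "With an estimated loss-to-follow-up rate of 20%, 480 participants will be recruited in total". With 1:1:1 allocation that is 160 per arm.

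The section on the primary outcome compares the week-8 response rates by a Z-test at 0.025 and states: "Any missing data at 8 weeks will be imputed using the baseline value". A response requires improvement from baseline. For pain, "The minimal clinically important improvement in pain is defined as 2 points in the NRS", and for function the threshold is 6 WOMAC points.

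The set to which this applies is described in three ways. The abstract names the intention-to-treat set. The section on analysis populations makes a modified full analysis set primary, which drops patients with no post-baseline measurement. The primary-outcome section says full analysis set. Efficacy is measured at weeks 4, 8, 16 and 26.

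**The concern.** Dividing the required number by 0.8 is the right allowance when lost patients are removed: 128 of 160 remain, and their response rates are undiluted. It is not the right allowance when lost patients stay in the denominator as failures. A patient given the baseline value has zero change, which can meet neither the 2-point nor the 6-point threshold. Both response rates are then multiplied by the retained fraction, and so is their difference. The extra 32 patients per arm only partly make up for this.

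MA vs SA is the comparison planned at the 20-point difference, and it is one of two primary hypotheses. A non-significant MA result would be read against a stated 80% power for 20 points, when the contrast actually analysed could be smaller and the power lower.

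**Working it through.** **Inputs.** Two-sided alpha 0.025 (z = 2.2414), power 80% (z = 0.8416), rates 70/60/40%, 128 per group, 20% loss and 480 in total (all from Sample size); baseline imputation (Analysis of the primary outcome); thresholds of 2 and 6 points (Primary outcome). The calculations below assume equal loss in both arms and that 70/60/40% apply to patients with week-8 data.

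**1. The plan's own figures reproduce.** For two proportions with pooled variance under the null,

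n = [2.2414 × √(2 × 0.5 × 0.5) + 0.8416 × √(0.6 × 0.4 + 0.4 × 0.6)]² / 0.20² = 117.5, that is 118 per group.

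With the continuity correction, (n/4) × [1 + √(1 + 4/(n × 0.20))]² = 127.3, that is 128. Then 128 / 0.8 = 160 per arm, and 3 × 160 = 480. The 128 therefore includes a continuity correction; the Z-test in the analysis section is named without one. Results below are given as uncorrected / corrected.

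**2. All 20% lost by week 8, all imputed.**

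- MA: 0.8 × 60% = 48%
- SA: 0.8 × 40% = 32%
- Difference: 16 points, 160 analysed per arm

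Exact enumeration of the pooled Z-test at 0.025 gives power of 76.0% / 72.3%. The normal approximation gives 75.5% / 71.7%. For scale, 80% power at 48% vs 32% would need 177 / 190 per arm.

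**3. 20% lost by week 8, with a share f of the losses before any post-baseline measurement.** Those patients drop out of the modified full analysis set. The number analysed is 160 × (1 − 0.2f), and the fraction of it imputed is q = 0.2(1 − f)/(1 − 0.2f). The rates become 60% × (1 − q) and 40% × (1 − q).

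| f | n per arm | MA vs SA | Difference (points) | Exact power |
|---|---|---|---|---|
| 0% | 160 | 48.0% vs 32.0% | 16.0 | 76% / 72% |
| 25% | 152 | 50.5% vs 33.7% | 16.8 | 77% / 73% |
| 50% | 144 | 53.3% vs 35.6% | 17.8 | 80% / 76% |
| 75% | 136 | 56.5% vs 37.6% | 18.8 | 81% / 78% |
| 100% | 128 | 60.0% vs 40.0% | 20.0 | 85% / 82% |

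**4. Less than 20% lost by week 8, all imputed, 160 per arm.**

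| Lost by week 8 | MA vs SA | Exact power |
|---|---|---|
| 16% | 50.4% vs 33.6% | 80% / 77% |
| 15% | 51.0% vs 34.0% | 81% / 78% |
| 10% | 54.0% vs 36.0% | 85% / 82% |

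**5. EA vs SA in the full-dilution case.** 0.8 × 70% = 56% vs 32%, 160 per arm: 98% with or without the correction.

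**6. If the assumed rates already count missing patients as non-responders.** 60% vs 40% then applies to all 160 per arm, and power is 91% (89% corrected).

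**The case against.** A reader might infer that the trial simply fails to deliver 80% power for MA vs SA. The document does not support that, for three reasons, and all three stand.

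- **Timing.** The 20% loss carries no time point, and follow-up runs to week 26. Patients lost after week 8 have their primary endpoint and cause no dilution. With the uncorrected Z-test, 80% is kept if about 16% or fewer are lost by week 8, even when every one of them is imputed.
- **Analysis set.** Under the modified full analysis set, patients with no post-baseline measurement are excluded, which is what the inflation assumes. The 16-point difference is one end of a 16-to-20-point range. Nor can one say that 80% holds only if about half the losses come before week 4: a lower week-8 loss also preserves it, and with the continuity correction half is not enough (76%).
- **Meaning of the rates.** The 70/60/40% come from an earlier trial that is not shown. If missing patients were already counted there as non-responders, the dilution is built in and power is about 91%.

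It is also fair that neither 128 nor 480 is miscalculated, that the full-dilution loss under the uncorrected test is about 4 points of power for one of two comparisons, and that type I error is unaffected.

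What remains is the mismatch. The plan applied the full 20% to a calculation for the week-8 endpoint, so testing it at 20% uses the plan's own premise. On that premise, 80% depends on conditions that the document does not state.

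**Conclusion.** The concern holds in conditional form. The loss allowance and the primary imputation rule rest on different assumptions about lost patients, and the stated 80% power for MA vs SA makes no allowance for the difference. At 20% week-8 loss with everyone kept in the analysis, as under the abstract's intention-to-treat set, power is about 76% (72% on the continuity-corrected basis behind the 128) for an analysed difference of 16 points. Under the modified full analysis set it lies between that and about 85% (82%), depending on how early patients are lost.

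These figures rest on equal loss across arms and on 70/60/40% being rates among patients with week-8 data. The document neither confirms nor excludes the second assumption. The point concerns MA vs SA only.

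**What to change.** In the sample-size paragraph:

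- Replace the unconditional 80% for MA vs SA with the power under the planned analysis: about 76% (72% with continuity correction) at 20% week-8 loss with all imputed, together with the ranges above for early exclusion and for lower week-8 loss. Give about 98% for EA vs SA.
- State the loss expected by week 8, as distinct from loss over the whole follow-up, and name the analysis set to which the power refers, in agreement with the abstract and the analysis sections.
- Have the authors state whether the 70/60/40% already count missing patients as non-responders. This is for them to say from the source trial. If so, power for MA vs SA at 160 per arm is about 91%.

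The cost is one paragraph and, unless the rates already include missing patients, a possibly less favourable power figure. The document reports that all 480 patients have been randomised; no further enrolment is proposed, and the test and the imputation rule need not change.

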### Statistical analysis

#### Statistical analysis population

A modified full analysis set, a per-protocol set, and a safety set will be used in this trial. The modified full analysis set will consist of all randomized participants who have at least one post-baseline measurement according to the modified intention-to-treat principle. The modified full analysis set will be the primary analysis set, and all analyses will be conducted for this population if not otherwise stated. Analyses of the modified full analysis set will provide an estimate of the effects of EA and MA.

The per-protocol set will include those who complete the treatment and follow-up on time according to the protocol without major violations. Major violations of the protocol will be judged during the blinded audit of the data. They include but are not limited to not meeting the inclusion criteria, meeting the exclusion criteria, receiving other treatments that might affect the symptoms of KOA during the trial, and completing <20 sessions of acupuncture. The per-protocol set will be the secondary analysis set and will be used for the sensitivity analyses.

All those who are randomized and have received at least one session of acupuncture will be defined as the safety set, which is used for the safety analyses.

#### General analysis principles

All data will be summarized by treatment group. Numbers (percentages) will be used to describe categorical data. Either means (standard deviations) or medians (interquartile ranges) will be used for quantitative data depending on whether the variables are normally distributed. If not otherwise stated, the significance level will be set at 0.05. The Bonferroni method will be used to adjust the significance level for multiple comparisons for the primary outcome. The conclusions will be based on the analysis of the primary outcome, and all secondary outcomes will be analyzed to support the primary analysis. All analyses will be carried out using SAS 9.3 (Cary, NC).

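### Holm's step-down would control the same 5% family-wise error as the fixed Bonferroni 0.025 and never have less power; at the planned rates MA vs SA would gain about 4 to 5 points

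*SAP article*

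**What the plan says.** Three sections of the SAP article state the multiplicity rule, and they agree.

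- *Sample size*: "With a two-sided significance level of 2.5% and power of 80%, 128 participants in each group will be required", and the 2.5% level "is a Bonferroni-adjusted alpha level as per the two predefined primary comparisons: EA vs. SA and MA vs. SA".
- *General analysis principles*: "The Bonferroni method will be used to adjust the significance level for multiple comparisons for the primary outcome".
- *Analysis of the primary outcome*: "The significance level will be adjusted at 0.025 for multiple comparisons using the Bonferroni method".

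None of them lets the level for one comparison depend on the result of the other. The planning rates are also in *Sample size*: "the response rates for the EA, MA, and SA groups were assumed to be 70%, 60%, and 40%, respectively". The size is set "to detect a difference as small as 20% between each acupuncture group and the control group", which is the MA vs SA contrast (60% against 40%). The Table 2 shell shows 95% confidence intervals for the pairwise differences.

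**The concern.** With two hypotheses, a fixed 0.025 for each is not the most powerful simple rule that keeps family-wise error at 5%. Holm tests the smaller P value at 0.025 and, if that is rejected, the larger at 0.05. It needs no ordering of EA and MA and no added assumption.

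Under the plan's own rates EA vs SA is almost sure to be rejected, so Holm would nearly always test MA vs SA at 0.05. Bonferroni keeps it at 0.025. MA vs SA has the smaller assumed effect and sets the sample size, and the article bases its conclusions on the primary outcome. What is at stake is some power on that comparison, given up with no gain in family-wise error control.

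**Working it through.** **Inputs.** Response rates 70/60/40%, two-sided 0.025 per comparison, 80% power, 128 per arm, 20% loss and 480 in total (*Sample size*); 1:1:1 allocation (*Study design*); Z-test for proportions with the baseline value imputed for missing week-8 data (*Analysis of the primary outcome*).

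**1. Reproduce the plan's figure.** For 60% vs 40%, with z(0.9875) = 2.2414 and z(0.80) = 0.8416:

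n = [2.2414·√(2·0.5·0.5) + 0.8416·√(0.6·0.4 + 0.4·0.6)]² / 0.20² = (1.5849 + 0.5831)² / 0.04 = 117.5, so 118.

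With the continuity correction: (117.5/4)·[1 + √(1 + 4/(117.5·0.20))]² = 127.3, so **128**. Then 128/0.80 = 160 per arm, and 3 × 160 = **480**. Both stated figures reproduce.

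**2. Error control.** Write P₁ and P₂ for the two P values.

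- Both nulls true: any Holm rejection needs min(P₁, P₂) ≤ 0.025, with probability at most 0.025 + 0.025 = 0.05 under any dependence.
- One null true: rejecting it needs its own P ≤ 0.05, with probability at most 0.05.
- Every Bonferroni rejection has P ≤ 0.025, and Holm rejects it too. Power therefore cannot fall.

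**3. Closed-form check at 128 per arm, MA vs SA.** Power = Φ{[0.20·√128 − z·√0.5]/√0.48}. With z = 2.2414 this is Φ(0.978) = 83.6%. With z = 1.9600 it is Φ(1.266) = 89.7%. The difference, 6.1 points, is what moving from 0.025 to 0.05 is worth under the normal approximation.

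**4. Simulation.** Three binomial arms with a shared SA arm, pooled two-sided Z-test, at least 1,000,000 trials per row; the last digit can move by 0.1.

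| Scenario (EA/MA/SA) | n per arm | EA rejected at 0.025 | MA vs SA, Bonferroni | MA vs SA, Holm | Gain (points) |
|---|---|---|---|---|---|
| 70/60/40% | 128 | 99.7% | 84.9% | 90.0% | 5.1 |
| 70/60/40%, all observed | 160 | 99.9% | 90.9% | 95.0% | 4.2 |
| 56/48/32%, all 20% lost by week 8 and scored as failures | 160 | 98.5% | 76.0% | 83.0% | 6.9 to 7.0 |
| 60/60/40% | 128 | 84.9% | 84.9% | 88.5% | 3.6 |
| 50/60/40% | 128 | 27.7% | 84.9% | 85.4% | 0.5 |
| 40/60/40% | 128 | 2.6% | 85.0% | 85.1% | 0.15 |

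The third row multiplies each planned rate by 0.8: an imputed baseline value means zero change, which cannot meet the responder thresholds. If the test itself carries a continuity correction, the gain at the planned rates is 5.9 points at 128 (81.7% to 87.6%) and 5.0 points at 160 (88.7% to 93.8%).

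At 40/40/40% the chance of at least one false rejection is 4.8% under both rules. At 70/40/40% the false rejection rate for MA rises from about 2.6% to 4.8%, still within the 5% family-wise limit.

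**The case against.** **Bonferroni is not an error here.** It is valid, fully pre-specified and the same in all three sections, and 128 was calculated at that level. MA vs SA has about 85% power at 128 evaluable per arm, so most of the points at issue lie above the planned 80%. All of this stands.

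**A reader might infer that Bonferroni leaves MA vs SA below 80% and that Holm is needed to restore it.** The documents do not support that. The 76% figure requires the whole 20% loss to occur by week 8 and every lost participant to be kept as a non-responder. The article does not tie the 20% to week 8, and follow-up runs to week 26. *Statistical analysis population* also keeps only those with at least one post-baseline measurement, and outcomes are first measured at week 4. If half of the 20% is excluded that way and half imputed, there are 144 per arm at 8/9 of the planned rates, and power is about 80% under Bonferroni and 86% under Holm. The article names the primary set differently in different places, so this is not settled. Any shortfall in the 76% case comes from the imputation rule, which is a separate matter.

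**Bonferroni has real merits.** The MA verdict does not depend on EA and would match a 97.5% interval. Under Holm, an MA P value of 0.03 is significant only if EA vs SA is rejected. This stands as a cost of the change. The Table 2 shell sets 95% intervals beside tests at 0.025, however, so the plan does not at present use the matching interval.

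**Timing.** The plan was approved on 30 October 2017 and all 480 participants had been randomized by October 2018. Relaxing a primary decision rule that late needs a dated justification. This also stands, and the fix includes one.

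**Conclusion.** The point holds as an optional, inexpensive efficiency gain. It reveals no fault in type I error control or in the sample size. At the plan's own rates Holm adds about 4 to 5 points of power for MA vs SA with the plain Z-test (5 to 6 with a continuity correction), and up to 7 in the worst case for losses.

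It would be tempting to quote 5 to 7 points without conditions. That overstates the gain, which depends on EA being rejected: about 3.6 points if EA is also 60%, 0.5 if it is 50%, and about 0.15 if EA is no better than sham. What holds without condition is that Holm never has less power and keeps the family-wise error at 5%.

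**What to change.** Before unblinding, reword *General analysis principles* and *Analysis of the primary outcome* along these lines: the two primary comparisons will be tested by Holm's method; the smaller P value is compared with 0.025 and, if it is rejected, the larger with 0.05; if the smaller is not rejected, neither comparison is declared significant.

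- Leave N at 480 and the *Sample size* calculation as it is; it is conservative under Holm.
- In Table 2, show 97.5% intervals for the two primary 8-week differences.
- Add a footnote: the second comparison can be significant with P between 0.025 and 0.05 while its 97.5% interval includes zero, and its verdict then depends on the other comparison.
- Date the change and record that it was made while the statisticians were masked. If that cannot be shown, keep Bonferroni as written.

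The cost is two reworded passages, two interval entries in Table 2, one footnote and a dated amendment note. No new participants, data or software are needed.
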